### **13.2.3 Blood Stocks Management Scheme**

Blood Stock Management Scheme (BSMS) collects data in relation to blood stock and wastage management from hospitals in England.

CTRU will request from BSMS hospital level datasets which will cover the period 12 months before and 12 months after the feedback is provided to NHS Trusts / Health Boards. Linkage of individual patients between the two datasets will not be possible. The data will be provided in electronic format, via a secure file transfer system, and will include the following variables:

- Month (Oct 2014 to July 2017)
- Laboratory (ID and name)
- Hospital (ID and name)
- Trust or Health Board (DoH Trust ID and name)
- Hospital Profile (i.e. hospital-level descriptive data) (incl. electronic/manual cross-matching, cross-match reservation period, cell salvage availability, Regional Transfusion Committee)
- Blood Group (O, A, B, AB +/-)
- Gross issue data for RBC, platelets (and adult FFP)

- Net issue data for RBC, platelets (and adult FFP)
- Wastage data for RBC, platelets (and adult FFP)
- Transfused data for RBC, platelets (and adult FFP)

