#### **13.2.4 Serious Hazard of Transfusion**

Serious Hazards of Transfusion (SHOT) is a UK wide haemovigilance scheme which collects anonymised data on adverse events and reactions associated with the transfusion of blood and blood components.

CTRU will request from SHOT fully anonymised patient level datasets which will cover the period 12 months prior to and 12 months after the feedback interventions begin. The data will be provided in electronic format, via a secure file transfer system, and will include the following variables:

- Unique Consecutive Incident ID
- Unique Consecutive Patient ID
- Speciality
- Hospital / Trust or Health Board
- Date of Transfusion
- Blood Components Transfused and/or Implicated Component(s)
- Source of Component (blood service donor, autologous, directed donation)
- Primary Diagnosis for the Component
- Transfusion Event (Adverse event, Pathological reaction, Transfusion Transmitted Infection, Pulmonary complication of transfusion)
- Type of Incident (Event, Near Miss, Right Blood Right Patient (RBRP))
- Date of Incident
- Status is: (i) pathological reaction which may not be preventable; (ii) probably or possibly preventable by improved practice and monitoring; or (iii) adverse event caused by error
- All datasets for Avoidable-, delayed- and under-transfusion (as per SHOT definitions).

These data will be used by the CTRU to derive baseline and outcome variables of interest for the trials at the randomised cluster-level. Once trust-level datasets have been linked, and prior to performing or reporting any analyses, all identifiers will be stripped and Trusts/Health Boards will only be identified by unique consecutive IDs.

For each incident type, data will be collected on investigations, treatments, support and outcomes so as to facilitate estimates of the costs and health outcomes of transfusion related adverse events for use as inputs into the health economic modelling. We will request data, already stripped of Trust and Health Board identifiers.

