### **16.3.4 Primary endpoint analysis**

For each topic independently, the patient-level binary primary outcome of unnecessary transfusions 12 months following randomisation will be analysed using logistic regression, with a random intercept for trust/health board, adjusting for design factors (that is, trust size, regional transfusion committee, and trust-level proportion of unnecessary transfusions at baseline), with contrasts for (1) enhanced vs. standard documents, (2) post-feedback support vs. no post-feedback support, and (3) the interaction between (1) and (2).

Unadjusted and adjusted intra-cluster correlations (ICCs) and corresponding 95% confidence intervals will be presented. We will report the estimates and two-sided 97.5% confidence intervals for the two main effects from this model.

In addition to sensitivity analyses relating to assumptions about the missing data mechanism we will also analyse the supportive outcomes that include a grey-area category using ordinal logistic regressions and look for consistency in the size, direction and interpretation of effect.

Following the analysis of each topic independently, a further analysis will be conducted using data from both audit topics. This analysis uses a bivariate patient-level binary primary endpoint outcome of unnecessary transfusions 12 months following randomisation and will be analysed using multivariate logistic regression, with a random intercept for trust/health board and will be adjusted for the same design factors as above and additionally controlled for audit topic. The model will then include contrasts for (1) enhanced vs. standard documents, (2) post-feedback support vs. no post-feedback support and (3) the interaction between (1) and (2). We will then fit all possible interactions between (1), (2), (3) and audit topic; we do this in order to get unbiased estimators for the general effects of interventions accounting for possible interactive effects between the two trials on the intervention effects. Unadjusted and adjusted intra-cluster correlations (ICCs) and corresponding 95% confidence intervals will be presented. We will report the estimates and two-sided 97.5% confidence intervals for the two main effects from this model and also for the interactions between (1) and (2) and audit topic.

The same sensitivity analyses will be run on this model as with the separate models.

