### **16.3.5 Secondary endpoint analyses**

The patient-level secondary endpoints for both trials covering volume transfused (both RBC and platelets) will be analysed using a Poisson random intercept regression model, with the same contrasts and adjusting for the same covariates as in the primary endpoint analysis. The trust-level secondary endpoints (volume transfused, number of SHOT-reportable incidents, and number of definitely, probably or possibly preventable incidents reported to SHOT within clinical specialities targeted by the audit) will be analysed using cluster-level analyses recognising the outcomes are all counts, again with the same contrasts and adjusting for the same covariates as in the primary endpoint analysis.

We will additionally analyse the supportive outcomes relating to the volume of transfused. The first two will act as sensitivity analyses for the trust-level analysis, indicating whether the size, direction and interpretation of the effect depend on the type of BSMS data summarised. The second three will act as a sensitivity analysis for the patient-level analysis, indicating whether the size, direction and interpretation of the effect depend on the stage in the operative process.

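### Trust-level blood-volume and SHOT outcomes are adjusted for the primary outcome's baseline and not for their own pre-feedback values, which the trial already obtains

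*Protocol*

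**What the plan says.** Protocol 16.1.2 lists as trust-level secondary outcomes the RBC units (both trials) and platelet units (haematology) derived from BSMS across all specialities, and two SHOT counts: all reports, and preventable reports in the audited specialities.

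Section 16.3.5 has these analysed by cluster-level methods for counts, "again with the same contrasts and adjusting for the same covariates as in the primary endpoint analysis". Section 16.3.4 lists the covariates of the primary analysis as "trust size, regional transfusion committee, and trust-level proportion of unnecessary transfusions at baseline".

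Section 9 makes trust size a three-level factor: tertiles of the number of cases a cluster submitted to that topic's baseline audit.

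Pre-feedback values of the same outcomes are obtained. For BSMS, 13.2.3 states: "CTRU will request from BSMS hospital level datasets which will cover the period 12 months before and 12 months after the feedback is provided". For SHOT, 13.2.4 requests datasets "which will cover the period 12 months prior to and 12 months after the feedback interventions begin", to be used to "derive baseline and outcome variables of interest for the trials at the randomised cluster-level". Table 1 marks both sources at Baseline and at Follow-Up.

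**The concern.** The primary outcome is adjusted for its own trust-level baseline. Carrying the same list over to the trust-level outcomes gives them the baseline of a different outcome. The share of audited patients with an unnecessary transfusion in one speciality need not say much about how many units the whole trust uses in a year, or how many incidents it reports. The natural predictor of next year's units or reports is last year's, and no section of the protocol enters it.

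Reduced blood use and fewer SHOT errors are named secondary objectives (6.2). Trusts can differ widely in annual volume for reasons unrelated to feedback. Variation left in the residual widens the confidence intervals, and a chance difference between arms in prior volume or prior reporting goes uncorrected.

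**Working it through.** **1. The plan's own figure.** The protocol gives power for the primary outcome only (16.2): 152 clusters, mean size 45 (17 to 68), ICC 0.05, cells 20/14/14/10%, two-sided 2.5%, 80% power. As a check:

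- The coefficient of variation of cluster size is taken as (68 − 17)/4/45 = 0.283.
- Design effect = 1 + ((0.283² + 1) × 45 − 1) × 0.05 = 3.38.
- Main effect on the logit scale = (0.429 + 0.382)/2 = 0.405.
- SE = ½ √[Σ 3.38/(1710 p(1 − p))] = 0.1296, with 38 × 45 = 1710 patients per cell.
- Power = Φ(0.405/0.1296 − 2.241) = 81%.

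With cluster sizes uniform over the range (CV 0.327), power is 80.5%. The stated figure reproduces, and nothing below changes it. The protocol gives no power figure, SD or correlation for the trust-level outcomes, so only relative precision can be assessed.

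**2. Formula.** Let ρ be the correlation between baseline and follow-up values of the outcome given the covariates already in the model. In a linear model on the log scale, adding the baseline multiplies the residual variance by 1 − ρ² and the SE by √(1 − ρ²). The gain is equivalent to multiplying the number of clusters by 1/(1 − ρ²). For log-link count models this is an approximation.

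| ρ (assumed) | Variance left | SE reduction | Equivalent factor on clusters |
|---|---|---|---|
| 0.3 | 0.91 | 5% | 1.10 |
| 0.5 | 0.75 | 13% | 1.33 |
| 0.7 | 0.51 | 29% | 1.96 |
| 0.8 | 0.36 | 40% | 2.78 |
| 0.9 | 0.19 | 56% | 5.26 |
| 0.95 | 0.10 | 69% | 10.3 |

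More than half the residual variance is removed only if ρ exceeds √0.5 = 0.707.

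**3. Which ρ is plausible for which outcome.** Partial correlations were simulated for 152 clusters on log counts. The model contained size tertile, 13 RTC levels, baseline proportion, both interventions and their interaction. Each count had Poisson noise plus year-to-year variation in the trust's underlying rate. The score behind the size tertile was allowed to correlate 0.5 to 0.9 with the trust's true level for volume, and 0.5 to 0.8 for SHOT. Every rate and SD here is an assumption.

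| Outcome | Assumed mean per trust-year | Between-trust SD (log) | Year-to-year SD (log) | Partial ρ | SE reduction |
|---|---|---|---|---|---|
| RBC volume | 10,000 units | 0.4–0.6 | 0.05–0.20 | 0.71–0.99 | 30–87% |
| All SHOT reports | 10–20 | 0.6 | 0.3 | 0.41–0.63 | 9–22% |
| Preventable SHOT reports, audited speciality | 0.5–2 | 0.6 | 0.3 | 0.12–0.28 | 1–4% |

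The outcomes differ because of Poisson noise. At 10,000 units it is negligible. At one or two reports a year it swamps the stable difference between trusts, so last year's count predicts little.

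**The case against.** **The SAP may settle this.** Section 16.3.6 leaves full details of the secondary analyses to the SAP, and 13.2.4 already says that SHOT baseline variables will be derived. But 16.3.5 does more than defer: it names the covariate set. A SAP that follows it inherits the omission, and one that departs from it should say so.

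**Trust size may already carry volume.** Sections 3, 5.3 and 13.2.1 describe size in terms of transfusion volume, which would put part of the predictor in the model. Section 9, which defines the factor actually used, takes tertiles of cases from one audit. Even a tertile built on a score correlating 0.9 with true volume left a partial correlation of 0.71 to 0.98 in the simulation.

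**The size of the gain is assumed.** This stands. It is also why a reader should not infer that most of the precision is lost for all these outcomes: that is plausible for volume but not for SHOT, which supplies two of the four surgical and two of the six haematology secondary outcomes.

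**Other inferences the protocol does not support:**

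- *The secondary objectives cannot be answered.* Randomisation keeps the estimates unbiased, and the protocol gives no SD from which to judge absolute precision.
- *Missing trust-level BSMS totals would be imputed.* Sections 16.3.1 and 16.3.3 speak of patients, in the main and primary analyses. Neither plans to impute trust totals.
- *The SHOT models wrongly lack an exposure term.* Section 16.3.5 does not exclude one, and this is ordinary SAP detail. An offset built from BSMS units could also lose the non-English clusters from the UK-wide SHOT analysis, if BSMS covers England only.

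**Conclusion.** The point holds in a limited form. As written, the trust-level volume and SHOT outcomes are adjusted for size tertile, RTC and the primary outcome's baseline proportion, and not for their own pre-feedback values, although those are obtained. The cost is precision and uncorrected chance imbalance. It causes no bias and leaves the primary analysis and the 152-cluster target untouched.

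For volume, a partial correlation of 0.7 to 0.95 implies a standard error about 30 to 70% smaller after own-baseline adjustment. For SHOT the gain is about 9 to 22% for all reports and 1 to 4% for speciality-specific preventable reports. These ranges rest on assumed correlations, counts and variances. The textual finding does not.

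**What to change.** In Protocol 16.3.5, and in the SAP, replace the reference to the primary covariates for the trust-level endpoints with an explicit list: trust size, RTC, and the trust's own value of that outcome over the 12 months before feedback. Use the log scale for RBC and platelet units and a suitable transform of the baseline count for SHOT (for example, log of the count plus 0.5, since zeros will occur). The baseline proportion of unnecessary transfusions drops out of these models and stays in the primary model. State how a cluster without a usable pre-feedback value is handled.

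The cost is a wording change, made before any outcome analysis so that it is pre-specified. It needs no new data request and no extra clusters. One covariate replaces another, so the models are no larger.

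A separate point for the sponsor to reconcile: 13.2.3 says BSMS "collects data in relation to blood stock and wastage management from hospitals in England", yet the same section lists a Health Board identifier and 16.2 relies on recruitment from all four nations. The clusters contributing to the BSMS outcomes should be stated. This limits baseline and follow-up alike and does not alter the fix above.

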### **16.3.6 Further secondary analyses**

Exploratory analyses will be conducted investigating mediators (e.g. fidelity: delivery, receipt and enactment) and moderators (e.g. trust size) of the main effects of the two feedback interventions in the surgical and haematological audits.

A number of exploratory sub-group analyses are planned which will be specified in detail in the SAP. These will include trust/health board and patient level factors such as trust size, TP involvement, surgical procedure and Haematological diagnosis.

Sensitivity analysis will be undertaken to investigate how contamination events, such as merging hospital trusts, might affect the size and direction of primary outcome measure.

Full details of all secondary analyses will be given in the Statistical Analysis Plan.

## **17 Safety**

The programme of research aims to improve adherence to recommendations, and therefore the interests of patients will be safe-guarded by the normal duties of care. Our interventions will comprise different ways of providing feedback to clinical teams on clinical performance and will be embedded within an existing national clinical audit programme. These interventions themselves will therefore not be directed at individual patients but we are assessing the indirect (or downstream) impact on patient care to determine the effectiveness of the interventions and thus inform future NHS quality assurance activities. A main patient benefit (and outcome) is measured by reduced exposure to the risks of unnecessary transfusions - we are not exploring the risk of under-transfusions.

Anyone delivering the interventions and in the trial team will have the opportunity to highlight any issues of concern with the trial team for further consideration. This will include escalation to the TSC and notifying the individual NHS Organisations in line with appropriate information and clinical research governance approval procedures.

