### **6.2 Secondary Objectives of the trials**

Secondary objectives are:

- To generate data to serve as inputs for an investigation of the relative cost-effectiveness of the two feedback interventions compared to usual NCA feedback in each audit topic from a NHS perspective
- To investigate whether the two feedback interventions reduce volume of blood products transfused (i) across specialities within NHS trusts and health boards and (ii) for patients treated in specialities targeted by transfusion topics, when compared to usual feedback, 12 months following randomisation
- To investigate whether two feedback interventions reduce the number of errors (defined in the Statistical Analysis Plan) reported to SHOT, when compared to usual feedback, 12 months following randomisation
- To explore whether there are differential predictors (or moderators) of the effects of the two feedback interventions when compared to usual feedback (i.e. subgroup effects)
- To explore the mechanisms by which the two feedback interventions affect outcome (i.e. mediators of the treatment effect)
- To explore whether the effect of the two enhanced feedback interventions when compared to usual feedback differs according to the transfusion topic

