### **16.1.2 Secondary endpoints**

For the surgical audit *secondary outcomes* are:

1. Total volume of allogeneic RBC transfused (Units at trust-level, from BSMS summed over blood groups and clinical specialities, calculated from net-issue minus wastage)
2. Total volume of allogeneic RBC transfused (Units at patient-level, from NCA summed over pre-operative, intra-operative and post-operative periods);
3. Total number of incidents reported to SHOT (Count at trust-level, from SHOT summed over clinical specialities and events, near misses and “right blood right patient” incidents)
4. Number of definitely, probably or possibly preventable incidents reported to SHOT within clinical specialities targeted by the audit (Count at trust-level, from SHOT summed over events, near misses and “right blood right patient” incidents)

For the Haematology audit *secondary outcomes* are:

1. Total volume of allogeneic RBC transfused (Units at trust-level, from BSMS summed over blood groups and clinical specialities, calculated from net-issue minus wastage)
2. Total volume of allogeneic RBC transfused (Units at patient-level, from NCA)
3. Total volume of platelets transfused (Units at trust-level, from BSMS summed over clinical specialities, calculated from net-issue minus wastage)
4. Total volume of platelets transfused (Units at patient-level, from NCA)
5. Total number of incidents reported to SHOT (Count at trust-level, from SHOT summed over clinical specialities, and events, near misses and “right blood right patients incidents)
6. Number of definitely, probably or possibly preventable incidents reported to SHOT within clinical specialities targeted by the audit (Count at trust-level, from SHOT summed over events, near misses and “right blood right patient” incidents)

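### The SHOT outcomes compared by arm are pooled counts that could mask a rise in delayed or under-transfusion reports, although the protocol already requests the data that would separate them

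*Protocol*

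**What the plan says.** **Safety position.** Section 7 says that the trials will assess safety outcomes alongside clinical, cost and process ones. Section 17 gives the main patient benefit as "measured by reduced exposure to the risks of unnecessary transfusions - we are not exploring the risk of under-transfusions".

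**Data requested.** Section 13.2.4 asks SHOT for records covering 12 months before and 12 months after the feedback begins. The list of variables ends with "All datasets for Avoidable-, delayed- and under-transfusion (as per SHOT definitions". On use, it says: "These data will be used by the CTRU to derive baseline and outcome variables of interest for the trials at the randomised cluster-level".

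**Objective.** Section 6.2 sets one direction: "To investigate whether two feedback interventions reduce the number of errors (defined in the Statistical Analysis Plan) reported to SHOT".

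**Outcomes.** Section 16.1.2 gives each trial two SHOT outcomes. One is "Total number of incidents reported to SHOT (Count at trust-level, from SHOT summed over clinical specialities and events, near misses and" right-blood-right-patient incidents. The other is "Number of definitely, probably or possibly preventable incidents reported to SHOT within clinical specialities targeted by the audit", summed in the same way. Neither is divided by type of incident. Section 16.1.3 lists no supportive or process variable for delayed or under-transfusion.

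**Analysis.** Section 16.3.5 says that the trust-level outcomes "will be analysed using cluster-level analyses recognising the outcomes are all counts".

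**The concern.** The interventions are meant to reduce transfusion. The intended effect is fewer unnecessary transfusions. The unintended effect worth watching for is blood given late or in too small an amount. Reports of the first kind should fall if the interventions work, and reports of the second kind might rise. A single sum over both cannot tell these movements apart, and the objective reads a lower sum as benefit.

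The audit data cannot fill the gap. Surgical audit cases have all had at least one transfusion (Section 16.1.1), and haematology audit records are built around a transfusion (Sections 13.3 and 16.1.1). A patient from whom blood was withheld altogether is not an audit case. SHOT is therefore the one source in the plan that could show such a change by randomised arm. At stake is a possible conclusion that the interventions left transfusion incidents unchanged or lower, with nobody having looked at the part of the count that matters most for safety.

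**Working it through.** The protocol states no figure for SHOT reports, so there is none to reproduce. The check has two parts.

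**1. Setting the sections side by side**

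- Can the categories be compared by arm? Yes. Section 13.2.4 requests them with trust identity and uses the data to derive cluster-level variables.
- Are they in the total? By inference. The outcome is the total number of incidents and no category is excluded, but the protocol does not name delayed or under-transfusion as components.
- Are they in the preventable count? This depends on SHOT's status classification of each report, which the documents do not describe in enough detail to settle.
- Are they separated anywhere by arm? No, not in Sections 16.1.2, 16.1.3 or 16.3.5.
- Do the other SHOT data help? No. The incident-level data for the economic model come without trust identifiers (Section 13.2.4), so they cannot be compared by arm.

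**2. Can the pooled count mask a change?**

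Let o, a and u be the yearly reports per trust for other, avoidable, and delayed or under-transfusion. Let f_a and f_u be the factors by which the last two change.

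Pooled rate ratio = (o + a·f_a + u·f_u) / (o + a + u).

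This equals 1 whenever a(1 − f_a) = u(f_u − 1), whatever the value of o.

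Approximate power for a Poisson log-rate-ratio Wald test, with K trusts on each side of a main effect:

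Φ( |ln(λ1/λ0)| / √(1/(Kλ0) + 1/(Kλ1)) − z ).

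Inputs:
- K = 2 × 38 = 76, from the 38 clusters per arm in Section 16.2.
- z = 2.241, from the two-sided 2.5% level. Section 16.3.1 sets that level for the primary outcome; it is borrowed here.
- All SHOT rates are assumptions, because the protocol gives none.
- No overdispersion and no covariates.

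Worked case: o = 10, a = 1.0, u = 0.5, f_a = 0.5, f_u = 2.
- Before: 10 + 1.0 + 0.5 = 11.5. After: 10 + 0.5 + 1.0 = 11.5. The ratio is 1.00, and the pooled test rejects only at its 2.5% error rate.
- Delayed or under alone: ln 2 = 0.693; standard error √(1/38 + 1/76) = 0.199; 0.693/0.199 − 2.241 ≈ 1.25; power about 89%.

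| o, a, u | f_a, f_u | Total | Pooled ratio | Pooled test rejects | Power, u alone |
|---|---|---|---|---|---|
| 10, 1.0, 0.5 | 0.5, 2 | 11.5 → 11.5 | 1.00 | 2.5% | 89% |
| 10, 1.0, 0.5 | 0.75, 1.5 | 11.5 → 11.5 | 1.00 | 2.5% | 38% |
| 10, 0.5, 0.25 | 0.5, 2 | 10.75 → 10.75 | 1.00 | 2.5% | 59% |
| 10, 0.5, 0.25 | 0.75, 1.5 | 10.75 → 10.75 | 1.00 | 2.5% | 19% |
| 10, 1.0, 1.0 | 0.5, 2 | 12 → 12.5 | 1.04 | 9% | over 99% |
| 10, 1.0, 0.5 | 1, 2 | 11.5 → 12 | 1.04 | 9% | 89% |

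In the first four rows the changes cancel by choice of rates. The fifth shows partial cancellation. The last has no offset at all: a doubling is simply diluted by other reports. Overdispersion would lower every power figure.

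**The case against.** **Declared scope.** Section 17 limits the scope openly and gives its basis: feedback goes to clinical teams, aims at adherence to recommendations, and leaves the normal duties of care in place. Requesting a dataset does not oblige anyone to make an endpoint of it. This has force, and the omission is a choice rather than a miscalculation. It does not explain why requested data on this question should stay unsplit when Section 7 promises safety outcomes.

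**Left to the statistical analysis plan.** Section 6.2 leaves the definition of errors to that plan, which is not at hand and might split the counts. That is possible. But the protocol itself fixes the outcomes as sums and rules the question out, so the point arises from what it states.

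**Escalation exists.** Staff can raise concerns with the Trial Steering Committee (Sections 17 and 19). That route depends on someone noticing a problem and gives no comparison by arm.

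**Stronger readings that a reader might infer.** The documents do not support these:
- *The protocol says that it adds delayed and under-transfusion reports to avoidable ones.* It does not say so. Inclusion in the total is inferred, and for the preventable count it is open.
- *The SHOT data serve only the totals.* They also feed the economic model (Sections 13.2.4 and 18.2), though not by arm.
- *The interventions will cause under-transfusion.* Nothing shows this. The target is transfusions categorised as unnecessary, and SHOT's definitions, which would show whether its reports capture a restrictive prescribing decision, are not given.
- *The Trial Steering Committee should see counts by arm as they accrue.* Section 7 keeps first-trial outcome results within the statistical team until second-trial results are available, Section 16.3.2 plans one final analysis, and under Section 25.1 the Chief Investigator and trial management members attend committee meetings.

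**Conclusion.** The point holds in a limited form. As the protocol stands, a rise in delayed or under-transfusion reports could be offset or diluted in the total SHOT count, and no other outcome compared by arm would show it. For the preventable count the same is possible but depends on SHOT's classification.

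The size is unknown. The calculations show only that masking is arithmetically possible across a range of assumed rates; they do not estimate how likely it is. Nor do they promise a powered test: under the assumptions tried, power for the separate count runs from 19% to over 99%, before any allowance for overdispersion. The primary outcome and its analysis are unaffected. This is a cheap improvement to safety reporting. It concerns which counts are reported and implies nothing about any transfusion threshold or clinical rule.

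**What to change.** - Keep both pooled SHOT outcomes in Section 16.1.2.
- Add to Section 16.1.3, for each trial, two trust-level supportive counts from the data already requested: (a) avoidable transfusion, and (b) delayed or under-transfusion, each by SHOT's definition. Label them descriptive safety outcomes.
- Report both by arm at the single final analysis, with rate ratios and confidence intervals, adjusted for the baseline count where numbers allow.
- Reword the statement in Section 17 rather than delete it. It should say that under-transfusion is examined only descriptively through SHOT reports and that the trials are not powered to exclude it.
- Keep results by arm within the statistical team until the final analysis, in line with Sections 7 and 16.3.2.

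The cost is one further table and a simple count model per trial, with no new data collection. The drawback is that events will probably be few and intervals wide. The report should say plainly that the absence of a visible difference is not evidence of safety.
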